# Trial Design

Local community mobilization coordinators (CMCs) working with the Global Polio Eradication Initiative (GPEI) will identify families with children in the target age-group (i.e. 6-11 months, 5-6-years, and 10-11-years). Surveillance Medical Officers (SMOs) will visit households of potential candidate families, explain the study to the parents or guardians, and facilitate transportation to one of the study sites for those interested to participate. Approximately 10 study sites will be chosen in areas identified as high-risk for poliovirus transmission.

At the study site, a physician will conduct a short interview and physical examination. After obtaining informed consent from the parents (and assent from children of age 10-11 years), the study participant will be assigned a study number and allocated to a study arm. For this, the parent or child will select a closed envelope that includes the study arm from a basket. Then a baseline blood sample collected by venipuncture, oral (crevicular) fluid, and stool samples will be collected before vaccine administration.

Note: crevicular fluid will not be collected in the 6-11 month age group because of the absence of teeth.

In a subset of children 10-11 years of age (~175-200 children) a second blood sample will be collected at 7 days by venipuncture for the ELISPOT test.

In all children, at 28 days, another blood sample by venipuncture, another oral (crevicular) fluid sample and a stool sample will be collected before the subjects receives the challenge vaccine (bOPV). Thereafter, at days 3, 7 and 14 stool samples will be collected. And finally, at day 56, another serum sample and oral fluid sample will be collected. At this time, having fulfilled the study requirements, the children will exit the study.

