## A diagram of the study design is shown below.

## A specific statement of primary and secondary endpoints:

The primary endpoint is reduction in excretion at days 3,7 and 14 post- challenge dose of vaccine poliovirus administered 28 days after a single dose of bOPV or IPV.

The secondary endpoints are:

- Increase of sIgA in gingival fluids and stools 28 days after a dose of bOPV or IPV.
- Increase in poliovirus antibody secreting cells (measured with ELISPOT) 7 days following a dose of bOPV or IPV.
- Seroconversion or antibody titer boosting 28 days following a single dose of bOPV or IPV.

A description of what kind of trial:

This is a randomized controlled unblinded trial.

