## A description of the measures taken to minimize/avoid bias, including randomization & blinding:

Since the vaccines are administered by different routes (oral for bOPV, and intramuscular for IPV), it is not possible to blind the investigators and the study staff (doctors, nurses, statisticians). However, all serum, oral fluid, and stool samples will be blinded to the laboratory investigators.

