## Maintenance of treatment randomization codes and procedures for breaking codes:

This trial is not blinded.

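### The arm is drawn from a basket with no numbering, log or bar on redraws, and is revealed before baseline blood, although a missed blood sample removes the child from the analysis

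*Protocol*

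**What the plan says.** The Trial Design section sets the order of the day-0 visit. A physician interviews and examines the child. Consent comes next: "After obtaining informed consent from the parents (and assent from children of age 10-11 years), the study participant will be assigned a study number". Allocation follows: "the parent or child will select a closed envelope that includes the study arm from a basket". Sampling comes after that: "Then a baseline blood sample collected by venipuncture, oral (crevicular) fluid, and stool samples will be collected before vaccine administration". The same section plans about 10 sites.

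On blinding, the protocol says "This is a randomized controlled unblinded trial". Clinical staff and statisticians know the arm, and only the laboratory is masked: "all serum, oral fluid, and stool samples will be blinded to the laboratory investigators".

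Two sections could have described the allocation safeguards. The one on measures against bias, whose title includes randomization, covers only blinding. The one on randomization codes says only "This trial is not blinded".

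On numbers, the sample-size section and Annex I plan 990 children in nine cells of 110 (three arms by three age groups), so that at least 89 per cell complete after an expected loss of 15-20%.

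On exclusions, the section on subject withdrawal drops from the final analysis any child who misses a scheduled blood sample, while a missed stool or gingival fluid sample does not exclude. Withdrawn children are not replaced. The sections on missing data and on selection of subjects restrict the analysis to children who complete the study with sufficient sera.

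**The concern.** In an open-label trial, allocation is the main protection against selection bias. A basket of loose envelopes has no sequence to audit: if a family dislikes its draw and takes another envelope, nothing in the described records would show it. The temptation is plausible, because the arms differ visibly.

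The order of steps opens a second route. The family knows the arm when the baseline venipuncture is requested. A parent whose child drew no vaccine, or drew the injection, may then decline the blood draw, and the analysis rule removes that child. Such a loss is a post-allocation exclusion that can be related to the arm. Had blood been taken first, a refusing child would simply never have been allocated.

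**Working it through.** **1. Safeguards, section by section.**

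| Safeguard | Where it could appear | What is there |
|---|---|---|
| Numbered sequence, opaque sealed envelopes | Trial Design; measures against bias | Closed envelopes in a basket; nothing more |
| Who prepares and holds the allocation | Randomization codes | Only that the trial is not blinded |
| Rule on returned or second envelopes | Trial Design | None |
| Separate series by age group or site | Trial Design; Annex I | Target of 110 per cell; no mechanism |
| Record of the draw | Day 0 case report form | Vaccine administered, lot and time; no field for envelope number, arm drawn or time of draw |

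The Day 0 form records the vaccine given, with no vaccine as one option. Unless the study number encodes the arm, which the protocol does not say, a child who drew a vaccine and declined it would look on this form like a control.

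**2. The plan's own figure.** Inputs from Annex I: excretion 0.30 v 0.10, two-sided alpha 0.05, power 0.90.
- Unpooled formula: n = (1.960 + 1.282)² × (0.30×0.70 + 0.10×0.90) / 0.20² = 10.507 × 0.30 / 0.04 = 78.8.
- Continuity correction: n' = (n/4) × (1 + √(1 + 4/(n×0.20)))² = 88.5, which rounds up to the stated 89.
- The pooled formula gives 82 without and 92 with the correction. Nothing below depends on which was used.
- After loss: 110 × 0.85 = 93.5 and 110 × 0.80 = 88.

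**3. Exclusion bias.** Let a share L of one arm be lost, and let the lost children's excretion differ from that of the retained children by D. The full-arm rate is (1−L)r + L(r+D) = r + L×D, so the retained rate r is off by L×D. L is the planned loss; D is an assumption, because the protocol gives nothing on it.

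| Loss L in one arm | D = 10 points | D = 20 points | D = 30 points |
|---|---|---|---|
| 15% | 1.5 | 3.0 | 4.5 |
| 20% | 2.0 | 4.0 | 6.0 |

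These are points of shift in one arm, against a target difference of 20. They put the entire planned loss in one arm and none in the comparator. Day-0 refusals would be only part of that loss, so the share that the order of steps can cause is smaller.

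**4. Chance imbalance.** Assume, since the text does not say, one pool of 990 envelopes (330 per arm) shared by all ages.
- Cell SD = √(330 × 1/3 × 2/3 × 660/989) = 7.0, a 95% range of about 96-124.
- By simulation, the smallest arm within an age group has median 103 (95% range 93-109). With independent random draws it has median 102 (90-108).
- Power at 0.30 v 0.10 with 20% loss (pooled test, no continuity correction): 0.919 at 88 v 88 completers. At a lopsided 72 v 96 completers (90 v 120 enrolled) it is 0.904 if the control arm is the smaller and 0.898 if the vaccinated arm is.
- Averaged over 20,000 simulated pools, power is 0.918 (95% range 0.901-0.933), against 0.919 for exact balance. With a continuity correction the two are 0.885 and 0.886.

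**The case against.** Several stronger readings are tempting, and the document does not support them.

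- **That arms are unbalanced by age group.** The protocol plans 110 per age group and arm. What is missing is the mechanism. Baskets may be kept separate by age; the text does not say. The design diagram was not available for this check and might show more.
- **That the basket leaves the trial underpowered.** The smallest of nine cells, under an assumed single pool, averages about 100 children, or 80-85 after loss. That is below 89, but exact balance with 20% loss already gives 88. The comparator is not also at its minimum, and power stays at about 0.90.
- **That allocation is being subverted or that refusals will occur.** Examination, consent and assent precede the draw. The family draws, not the staff, which limits direct staff selection, and the envelope is closed. Redraws are neither provided for nor ruled out. Handling rules may sit in the study operating procedures mentioned under Auditing. Refusals can occur; no rate is given.
- **That reordering day 0 cures arm-dependent exclusion.** By days 28 and 56 families know their arm whatever the day-0 order, and the completer rule applies there too.
- **That permuted blocks are a free improvement.** Three age groups by about 10 sites make about 30 strata of some 33 children (990/30, if sites recruit equally). Staff in an open-label trial can predict the end of a fixed block, which a well-shuffled basket avoids.

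What remains is narrower. The protocol itself fixes the allocation step, that step carries no stated safeguard or audit trail, and it sits ahead of a sample whose absence removes the child. The allocation procedure belongs in the protocol, so an analysis plan that is not shown would not be expected to supply it.

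**Conclusion.** The point holds as a weakness of procedure. As written, the draw allows untraceable redraws, states no way of delivering 110 per age group and arm, and lets day-0 exclusions depend on the arm. The consequence is possible selection and exclusion bias in a trial with no masking outside the laboratory.

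The size of that bias cannot be derived from the protocol. The 1.5-6 point range rests on an assumed difference in excretion of 10-30 points and on the whole planned loss falling in one arm. It is a scale for judging the issue against the 20-point target, not an estimate. Chance imbalance in cell sizes is not a material part of the case: under a single undivided pool, mean power changes by about 0.001. The sample size needs no change.

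**What to change.** Rewrite the allocation step in Trial Design, and repeat it under the section on measures against bias:

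1. Allocate from a pre-generated list, stratified at least by age group and by site if practical, with varying block sizes that are not disclosed to site staff.
2. Issue sequentially numbered, opaque, sealed envelopes, opened strictly in order. Log each opening against the study number, and state that an opened envelope cannot be exchanged.
3. Open the envelope only after consent, eligibility, baseline blood and, where the age group provides it, oral fluid are complete. Baseline stool may follow if it cannot be produced on site, since a missed stool sample does not exclude a child.
4. Add envelope number, arm allocated and time of opening to the Day 0 form.

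The cost is preparing the list and envelopes, a few form fields and a reordering within one visit. There is no extra visit and no change to the 110 per cell. Families lose the visible draw. The change does not remove arm-dependent exclusions at days 28 and 56; those follow from the completer analysis set and need separate attention.

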## A diagram of the study design is shown below.

## A specific statement of primary and secondary endpoints:

The primary endpoint is reduction in excretion at days 3,7 and 14 post- challenge dose of vaccine poliovirus administered 28 days after a single dose of bOPV or IPV.

The secondary endpoints are:

- Increase of sIgA in gingival fluids and stools 28 days after a dose of bOPV or IPV.
- Increase in poliovirus antibody secreting cells (measured with ELISPOT) 7 days following a dose of bOPV or IPV.
- Seroconversion or antibody titer boosting 28 days following a single dose of bOPV or IPV.

A description of what kind of trial:

This is a randomized controlled unblinded trial.

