# Trial Objectives and Purpose

## Mucosal immunity:

- To compare baseline mucosal immunity (through different methods) among three age groups with several degrees of protection acquired through immunization:
  - Infants 6-11 months of age will have received a few OPV doses
  - Children 5-6 years of age will have received multiple OPV doses in campaigns and are expected to have the highest levels of mucosal and humoral immunity
  - Children 10-11 years of age will not have received booster OPV doses for > 5 years. They are expected to have high antibody titers but may have waned mucosal immunity.
- To determine whether one dose of bOPV or IPV significantly reduces excretion of poliovirus types 1 and 3, respectively, following a challenge dose with bOPV, compared to an unvaccinated control arm.
- To determine whether one dose of bOPV or IPV significantly increases sIgA in crevicular fluids and stool samples, and to examine whether the increase in specific SIgA in these specimens is correlated to a reduction in excretion of Sabin poliovirus types 1 and 3 following the challenge with bOPV. This will allow evaluating the use of sIgA as a surrogate test for assessment of mucosal immunity.
- To determine the robustness of the mucosal immune response by study arm and age group, by measuring poliovirus antibody-secreting cells in an ELISPOT-spot assay 7 days after the administration of the study vaccine.

Humoral immunity:

- To determine whether one dose of bOPV or IPV will significantly increase seroprevalence and booster antibody titers compared to unvaccinated children.
- To assess whether one dose of IPV will significantly increase seroprevalence and antibody titers compared to a single dose of bOPV.
- To examine the correlations between antibody titers in blood and shedding of poliovirus after a challenge dose, for each vaccine study arm and age group.
- To examine the correlation between levels of IgA in serum and levels of secretory IgA in crevicular fluids and stool samples, before and after the booster vaccine dose, to gain further understanding on the mechanisms of mucosal immunity against poliovirus.
- To analyze correlations between levels of secretory IgA in crevicular fluids and stools and the ELISPOT test results, to better understand mucosal immunity against poliovirus.

Safety:

- To assess adverse events following vaccine administration.

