## The level of significance to be used:

We are seeking to show (a) a reduction in number of subjects excreting vaccine poliovirus following a challenge vaccine dose (bOPV) among those vaccinated with bOPV or IPV compared to the control group; (b) an increase in secretory IgA following vaccination with bOPV or IPV compared to a control group; and (c) an increase in seroprevalence or antibody titers following vaccination with bOPV or IPV compared to a control group.

We use a level of significance of 0.05 (two-tailed test) and a power of 90% to detect the │20%│difference in proportion of subjects shedding vaccine poliovirus after the challenge dose of bOPV(see annex I).

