# 7. To account for drop-outs and ensure that sufficient subjects will complete all study requirements, we will enrol a total of 990 subjects, 110 per age-group (6-11 mo, 5-6 years and 10-11 years) and per study arm (IPV, OPV and controls).

# ANNEX II

Analytic plan

1. The primary endpoint of the study is reduction in excretion of poliovirus following a challenge dose of bOPV in subjects who have received a single dose of bOPV or IPV.

2. We will use chi-square test to compare the proportion of study subjects that excrete virus/or not following the challenge, in each study arm.

3. To use a conservative measure of p, we will apply a two-tailed test. We will also prepare 95% confidence intervals.

4. We will use non-parametric tests to compare the (median) amount of virus excreted after the challenge in each study arm.

5. We will also use non-parametric tests to measure and compare the distribution of antibody titers in serum (only for those with a positive titer; i.e., >1:8), among study groups and before and after treatment.

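### The sIgA and ELISPOT endpoints are worded as rises after vaccination with no comparator, and Annex II sets a before-after titre test beside the between-arm test without saying which decides

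*Protocol*

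**What the plan says.** **Endpoint list (Trial Design, statement of primary and secondary endpoints).** For sIgA the secondary endpoint reads "Increase of sIgA in gingival fluids and stools 28 days after a dose of bOPV or IPV". The one for ELISPOT reads "Increase in poliovirus antibody secreting cells (measured with ELISPOT) 7 days following a dose of bOPV or IPV". The one for serum titres reads "Seroconversion or antibody titer boosting 28 days following a single dose of bOPV or IPV". None names a comparator. The primary endpoint in the same list does not name one either.

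**Trial Objectives and Purpose.** The sIgA objective begins "To determine whether one dose of bOPV or IPV significantly increases sIgA in crevicular fluids and stool samples" and names no comparator, although the excretion objective just before it names the unvaccinated arm. The ELISPOT objective is "To determine the robustness of the mucosal immune response by study arm and age group". The humoral objective does name the comparator: one dose of either vaccine "will significantly increase seroprevalence and booster antibody titers compared to unvaccinated children".

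**Statistics, level of significance.** Item (b) aims for "an increase in secretory IgA following vaccination with bOPV or IPV compared to a control group". Item (c) does the same for seroprevalence and titres. ELISPOT is not mentioned.

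**Statistics, description of methods, and Annex II.** The methods paragraph compares titre distributions between arms. Annex II item 5 compares them "among study groups and before and after treatment" and does not say which comparison decides.

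**The concern.** An increase after a dose can be tested in two ways: as a change from day 0 inside a vaccinated arm, or as a difference from the unvaccinated arm. Only the second uses the randomisation. The first cannot separate a vaccine effect from anything else that moves the measurement between the two visits.

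The protocol gives reasons to expect some movement:

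- The Preamble describes monthly high-coverage vaccination rounds and very efficient virus transmission in this setting, and the exclusion criteria do not bar campaign doses during the study.
- The ELISPOT procedure in Annex IX starts from fresh anticoagulated blood and shows no freezing step. As written, day-0 and day-7 samples are therefore run on different days, and run-to-run variation enters the rise directly.
- The same-plate rule in the efficacy methods covers the neutralisation assay only. No such rule is stated for sIgA.

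At stake are claims that a vaccine raises mucosal antibody or antibody-secreting cells. They matter because the trial also judges sIgA and ELISPOT as possible substitutes for the challenge test.

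**Working it through.** **1. The contrast stated for each endpoint.**

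| Endpoint | Endpoint list | Objectives | Level of significance | Methods / Annex II |
|---|---|---|---|---|
| sIgA | no comparator | no comparator | against control | no test given |
| ELISPOT | no comparator | by arm and age group only | not mentioned | no test given |
| Titres | no comparator | against unvaccinated | against control | between arms; Annex II adds before-after |

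One statement repairs the sIgA wording and none repairs ELISPOT. For titres the only loose end is the unranked pair in Annex II item 5.

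**2. The plan's own figure.** Annex I gives 89 per arm and age group for excretion of 0.30 v 0.10, two-sided alpha 0.05, power 0.90. The unpooled formula gives (1.960 + 1.282)² × (0.30×0.70 + 0.10×0.90) / 0.20² = 78.8, so 79. The continuity correction gives 79/4 × (1 + √(1 + 4/(79×0.20)))² = 88.7, so 89. Exact power with Fisher's test at 89 is 0.902. The figure reproduces, but it covers the primary endpoint only; no size or power is stated for the secondary endpoints. It is used below only as the number of children per cell.

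**3. Effect of a shared background change.** Assumptions, since the documents give no figure: no vaccine effect, and every arm shifts by d = 0.1, 0.2 or 0.3 SD of the within-child change. By the normal approximation,

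P(significant increase in a vaccinated arm) = 1 − Φ(1.96 − d√n).

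- n = 89 (√n = 9.434): 1 − Φ(1.017) = 0.155; 1 − Φ(0.073) = 0.471; 1 − Φ(−0.870) = 0.808.
- ELISPOT, assuming 175–200 children split equally over three arms (58–66 per arm; n = 62, √n = 7.874): 0.120, 0.350 and 0.656.

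In the between-arm difference the shared shift cancels, so an upward false positive stays at 2.5%.

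The chance that a vaccinated arm is significant and control is not, which would look convincing, is u(1 − u), with u the probability above. At n = 89 this is 0.131, 0.249 and 0.155.

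**4. Check with rank tests.** Simulation of 2,000 trials per setting, normal changes, two-sided 0.05:

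| Shift (SD) | Signed-rank, n = 89 | Signed-rank, n = 58 to 66 | Mann–Whitney v control, n = 89 |
|---|---|---|---|
| 0 | 4.0% | 4.4–5.0% | 6.0% |
| 0.1 | 14.6% | 10.4–12.0% | 5.8% |
| 0.2 | 45.7% | 32.4–35.2% | 5.2% |
| 0.3 | 77.4% | 60.0–66.6% | 4.8% |

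**5. Binary version, n = 89.** Suppose 5% of children fall and 10%, 15% or 20% rise for reasons shared by all arms. An exact McNemar test within the arm is significant in 15.6%, 48.8% and 78.5% of trials. A between-arm chi-square on the proportion rising stays at about 5%.

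**The case against.** The best reply is that an endpoint list is not a test specification. The primary endpoint in the same list also omits its comparator, yet it can only be a between-arm contrast, because no challenge precedes day 28. The trial is described as randomised and controlled, a within-child rise can be the endpoint and still be compared between arms, and the significance section completes the sIgA wording. This largely stands. A reader might infer that the protocol commits itself to before-after tests of sIgA and ELISPOT, or gives all three endpoints two contradictory definitions. It does neither: the sIgA wording is incomplete in two places and completed in one, ELISPOT lacks a comparator, and titres have a between-arm contrast in four places.

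The background-change argument also has limits:

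- The trial design justification gives the campaign age range as under 5 years, so direct campaign doses concern mainly the 6–11 month group. Crevicular fluid is not collected in that group, and ELISPOT is confined to children of 10–11 years.
- Same-plate testing of each child's sera limits assay drift for titres.
- sIgA is graded high, medium or low, and seroconversion and boosting are binary, so a normal model of change is only a rough guide.

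Finally, test details for a secondary endpoint may be left to a separate analysis plan. That is so, and the absence of a named sIgA or ELISPOT test is not the point here. The point is what the protocol itself fixes: endpoints that a within-arm rise would satisfy, and an annex that lists two contrasts for titres with no order between them.

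**Conclusion.** The point holds in a limited form. As worded, the sIgA and ELISPOT endpoints could be declared met by a rise within a vaccinated arm, and Annex II item 5 permits the same for titres. Such a rise cannot distinguish the vaccine from background or run-to-run change.

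The rates of 15%, 47% and 81% rest wholly on assumed shifts. A reader might take them as this trial's false-positive rates; the documents do not support that, and with no shift the before-after test keeps its nominal level. The mechanism is certain and its size here is unknown.

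Only secondary endpoints are touched. The wording should still be corrected, because sIgA and ELISPOT are being assessed as markers of mucosal immunity and the correction costs little.

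**What to change.** In the endpoint list, in the sIgA and ELISPOT objectives and in Annex II, state that the deciding contrast for each secondary endpoint is each vaccine arm against the unvaccinated arm within age group, at day 28 (day 7 for ELISPOT). Adjust for the child's day-0 value by a method that suits the scale:

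- graded sIgA: an ordinal model, or a rank test stratified by baseline category;
- titres: a rank-based adjustment, or one that allows for censoring at the assay limits;
- seroconversion or boosting: a between-arm comparison of proportions.

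Label before-after changes within an arm as descriptive.

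State also that the day-7 ELISPOT subset includes control children. The Trial Design section does not say so, and the size does not settle it: 175–200 is below both the 3 × 110 = 330 children enrolled in that age group and the 2 × 110 = 220 of them in the vaccine arms. If controls were left out, no comparison with control would be possible.

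Cost: for sIgA and titres, wording and slightly more analysis work, since day-0 and day-28 samples are already planned in every arm. For ELISPOT, wording only if controls are already in the subset. The between-arm test has less power than a paired test when there is no background change. For example, with a true effect of 0.3 SD of the change at 89 per arm, unadjusted power is 1 − Φ(1.96 − 0.3√(89/2)) = about 52%, against 81% for the paired test. Adjustment for day 0 can recover part of this.
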